### Intervention group

Patients in the intervention group will be randomised to a shared care programme with joint participation in the delivery of care by the GP and the outpatient clinic. It comprises four visits a year, namely one annual comprehensive check-up at the outpatient clinic and three quarterly visits at their GP (Fig. 3). The annual comprehensive check-up will include biochemical tests, electrocardiogram, fundus photography, feet examination including biothesiometry to detect early signs of peripheral neuropathy, consultations with a diabetes nurse focusing on life-style intervention and compliance, and an endocrinologist focusing on an individualised optimal pharmacologic treatment, prevention of complications and a target-oriented treatment plan for the following year (Fig. 2). All the procedures will be performed the same day during a two-to-three hour visit. The first visit at the GP’s office after the annual comprehensive check-up will be carried out by the GP. The following two visits can be handled by either the GP or the practice nurse according to standard procedures at the local primary healthcare clinic. No further interventions related to the trial will be conducted in the general practices, as healthcare professionals should manage the delivery of care as usual. In order to secure transition of knowledge from the outpatient clinic to the GP, a copy of the medical record statement will be sent electronically to the GP after the annual comprehensive check-up. This report includes a plan and targets for the T2D treatment on different key parameters such as HbA_1c_ and blood pressure. Furthermore, we will use a direct electronic communication system to enable communication across the interface of the different GPs and the outpatient clinic. This is a well-established secure communication channel for exchanging messages, which is available for all healthcare professionals in both the primary and secondary healthcare sector in the Capital region of Denmark. In case of urgent problems or questions, the GPs can call a Diabetes Hotline, which can be called every day during working hours and is answered directly by an endocrinologist in the outpatient clinic. Patients in the intervention group will receive a leaflet and verbal information about the free lifestyle rehabilitation services offered by their local municipality. This includes patient education, physical activity, dietician consultations, and smoking cessation courses. Furthermore, they will be informed that questions concerning T2D, in the period between the annual comprehensive check-ups, should be addressed to the health professionals at the GP’s office.

**Fig. 3 Fig3:**
[figure not shown]
Schematic diagram of the intervention

### Control group

Patients in the control group will be attending a well-established visiting algorithm consisting of four visits a year with the diabetes team at the outpatient clinic, namely an annual comprehensive check-up, identical to the one received by the intervention group, and three quarterly visits. During the three quarterly visits, they will be seen by an endocrinologist according to the visiting algorithm (Fig. 3). Patients receiving usual care will be offered lifestyle rehabilitation services such as patient education, physical activity and dietician consultations at the hospital. Any questions or uncertainties concerning their T2D should be addressed to the healthcare professionals at the outpatient clinic.

### Study data

All study data will be collected in connection with the annual comprehensive check-up in the outpatient clinic at the baseline-screening visit, as well as 12, 24 and 36 months after baseline. Data will be obtained from medical records, laboratory databases, self-reported patient questionnaires and face-to-face by the primary investigator who does not take part in the treatment or care of the patients. All data will be registered in an Epidata database [32]. The database is stored at Gentofte Hospital in a secure purpose-designed password-protected web-based file system.

The primary outcome is the difference in mean HbA_1c_ between the two groups measured at 12-, 24- and 36-months follow-up. The secondary outcome is the proportion of patients who meet the set of Danish standard indicators reflecting quality of care at 12, 24 and 36 months follow-up [33]. These indicators cover seven areas, including HbA_1c_, blood pressure, low density lipoprotein, albuminuria, fundus photography, foot examination, smoking status and proper treatment and control of these factors. The indicators are primarily based on process variables, but do include a few numerical variables.

Other outcomes are listed below:

*Clinical characteristics:* Blood pressure, weight and body mass index.

*Diabetes-related laboratory parameters and characteristics:* C-peptide, insulin, lipids, liver function tests, kidney function tests, electrolytes, coagulation factors, thyroid-stimulating hormone, cardiovascular biomarkers, vitamin D, urine albumin/creatinine ratio, and registration of diabetes-related medication.

*Healthcare professionals’ experiences with shared care:* A questionnaire evaluating the experiences of the participating GPs and the endocrinologists after the completion of the 12- and 36-month follow-up periods.

*Patient-reported outcomes:* Estimation of general quality of life, diabetes-related symptoms, alcohol consumption patterns as well as patients’ experiences of family network and function.

The four questionnaires used are:

*Short Form 36 (SF-36):* SF-36 is a generic self-administered patient questionnaire measuring quality of life [34, 35]. The 36 items of SF-36 are grouped into eight domains: physical function, physical limitations, bodily pain, general health, vitality, social function, emotional limitation and mental health. The answers of each scale are transformed into a 0–100 score. An increase in the score indicates less disability. The eight domains can be divided into physical and mental health summary scales, respectively. SF-36 has been validated and is reliable in a range of languages, including Danish [36].

*Diabetes Symptom Checklist – Revised (DSC-R):* DSC-R is a disease-specific questionnaire measuring the occurrence and perceived burden of T2D-symptoms [37]. It comprises 34 items grouped into eight domains: hyperglycaemic, hypoglycaemic, psychological-cognitive, psychological-fatigue, cardiovascular, neurological-pain, neurological-sensory, and ophthalmologic [37, 38]. It is a self-administered questionnaire. For each item, patients answer whether or not they have experienced the described symptom within the last 4 weeks, and if “yes”, they specify how troublesome the symptom has been on a 5-point Likert scale. Each domain is calculated by adding up the scores for each item (range, 1–5 points) and then divide the summed score by the number of items within the domain. A reduction in score indicates less diabetes symptom distress. DSC-R is a previously validated, reliable measurement instrument, sensitive to changes over time [38].

*The Alcohol Use Disorders Identification Test (AUDIT):* The AUDIT was developed on behalf of the World Health Organization as a screening tool for identifying persons with hazardous and harmful alcohol consumption patterns [39, 40]. It consists of 10 questions divided into three domains: hazardous alcohol use, dependence symptoms and harmful alcohol use. Each question has three or five response options and each answer triggers a score of 0–4 points. The scores are added up to a total score ranging from 0 to 40 points. Seven points is defined as the cut-off representing an alcohol problem. A higher score indicates a more hazardous and harmful alcohol consumption pattern [39].

*Family assessment measure III (FAM-III):* FAM-III is a self-administered questionnaire assessing family functioning. It consists of three 14-item questionnaires; the general scale examines the general health of the family; the dyadic relationship scale assesses how family members view their relationship with each other; and in the self-rating scale, individuals rate their own functioning within the family. Each item is answered on a 4-point Likert scale, giving a total score of 0–168. Low scores indicate a strong and well-functioning family, while high scores indicate a problematic and dysfunctional family. It is a useful, validated instrument for measuring family functioning during the course of treatment [41].

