### Randomisation

Patients will be randomised to the intervention or control groups in a 1:1 ratio. The randomisation sequence is computer generated by a statistician, who is not participating in the study. A secretary in the outpatient clinic will handle the script and instructions. The secretary will prepare sealed envelopes in accordance with instructions, and the envelopes will be stored and administered by the secretary during the period of inclusion. There will be an envelope prepared for each GP, and we will randomise the patients in blocks of two since we aim at each GP having an equal number of patients in the intervention and control group. The randomisation will be performed immediately after the baseline screening visit. Healthcare professionals involved in the study, including the principal investigator, will be blinded to the randomisation process. The allocation will be revealed after the screening visit. Further blinding is not possible due to the circumstances of the intervention.

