### Population size calculation

A power calculation was conducted according to criteria for non-inferiority trials [42, 43], and based on the primary outcome measure Hb_A1c_ at 12-month follow-up. The non-inferiority margin was set at 0.4 % (1 % is approximately 11 mmol/mol) based on both clinical judgement and a guideline from the European Medicines Agency identifying the non-inferiority margin for HbA_1c_ above 0.3 % (3 mmol/mol) [44]. The standard deviation of HbA_1c_ was set at 10 mmol/mol, based on a recent study on patients with risk stratification level 2 attending our outpatient clinic [31]. With a non-inferiority margin at HbA_1c_ 4.4 mmol/mol, an alpha of 0.05 and a power at 0.8, as well as an estimated dropout rate of 10 %, the sample size has been estimated to 140 participants.

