### Statistical analysis

We will present and compare the baseline demographics as well as clinical and diabetes-related characteristics of the intervention and the control group. The statistical comparison will be conducted on the basis of *t* tests or analysis of variance as appropriate for comparing means and χ^2^ tests for categorical or binary data. The primary outcome will be tested by constructing a 90 % two-sided confidence interval for the difference of the means of HbA_1c_ between the intervention and the control group. We use the lower bound to determine non-inferiority. Other outcomes will be tested with superiority analyses such as linear or logistic regression analysis. For observed differences we will consider a *P* value less than 0.05 as statistically significant.

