## Discussion

The overall objective of this study is to evaluate whether sharing general and specialised healthcare is comparable to the specialised care delivered in a hospital-based outpatient setting for patients with T2D who are at intermediate risk of or are already having incipient diabetic complications. The hypothesis is that the changes in HbA_1c_ at 12-, 24- and 36-month follow-up are comparable between the intervention and the control group. According to previous studies the evidence for shared care in different chronic diseases, including T2D, is not clear [20]. Testing new shared care models as a way of alternative organisation of care for patients with T2D is therefore important. The majority of studies on shared care for patients with T2D have been conducted 15–20 years ago. However, the increasing number of patients with T2D who are referred to the outpatient clinics as well as the development and improvements of electronic systems, clinical databases and communication channels during the last decades has made it highly relevant to test shared care models in new settings. Shared databases and electronic correspondence across the interface of the primary and secondary healthcare sectors are expected to blur the boundaries between the different healthcare sectors.

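### The primary HbA1c comparison is defined at 12, 24 and 36 months but sized for 12 months only, and the deciding visit is not named

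*Protocol article*

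**What the plan says.** Four places in the protocol article bear on which visit decides the primary question.

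- **Study data:** "The primary outcome is the difference in mean HbA_1c_ between the two groups measured at 12-, 24- and 36-months follow-up". No visit is put ahead of the others. The secondary outcome is given at the same three visits, so 24 and 36 months are not set apart as secondary.
- **Discussion:** "The hypothesis is that the changes in HbA_1c_ at 12-, 24- and 36-month follow-up are comparable between the intervention and the control group". All three visits appear again, now in terms of changes where Study data speaks of means.
- **Population size calculation:** the calculation is "based on the primary outcome measure Hb_A1c_ at 12-month follow-up". Its inputs are "With a non-inferiority margin at HbA_1c_ 4.4 mmol/mol, an alpha of 0.05 and a power at 0.8", "The standard deviation of HbA_1c_ was set at 10 mmol/mol" and "an estimated dropout rate of 10" per cent, leading to 140 participants.
- **Statistical analysis:** "The primary outcome will be tested by constructing a 90 % two-sided confidence interval for the difference of the means of HbA_1c". This describes one interval and names no visit.

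**The concern.** Alpha and power describe a decision rule. Here the outcome definition and the hypothesis imply a rule over three visits, while the sample size is built for a rule at one. The analysis section does not settle which applies.

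A three-visit definition can be turned into a verdict in at least two ways. Non-inferiority may have to be shown at every visit, or one visit may be enough. The first costs power and the second costs control of the false-positive rate. The three visits may also disagree, and the article does not say which of them then determines whether shared care is declared non-inferior.

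**Working it through.** **Inputs from the article.** Margin 4.4 mmol/mol, SD 10 mmol/mol, alpha 0.05, power 0.8, dropout 10%, total 140 (Population size calculation); two-sided 90% interval, that is one-sided 5% (Statistical analysis); "Patients will be randomised to the intervention or control groups in a 1:1 ratio" (Randomisation).

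**Assumptions not in the article.** The same correlation between every pair of visits, varied from 0 to 0.9; 63 evaluable per arm at every visit unless stated otherwise; the same SD and margin at each visit. Power is computed at a true difference of 0. False non-inferiority is computed at a true difference of 4.4 at all three visits.

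**Step 1. Reproduce the stated sample size.**
n per arm = 2 × [SD × (z₀.₉₅ + z₀.₈₀) / margin]² = 2 × [10 × (1.645 + 0.842) / 4.4]² = 63.9, so 64 per arm and 128 in total.
Dropout: 128 / 0.9 = 142.2, so 143; or 128 × 1.1 = 140.8, so 141. The stated 140 is within 3% of either. One-sided 2.5% would give 82 per arm and 183 in total, so the plan clearly used one-sided 5%.

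**Step 2. Power of one test with the planned number.**
140 × 0.9 = 126, or 63 per arm. Standard error = 10 × √(2/63) = 1.782. 4.4 / 1.782 − 1.645 = 0.825, and Φ(0.825) = 79.5%. A single 12-month test therefore delivers essentially what is stated.

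**Step 3. Two readings of the three-visit definition.** With three equally correlated normal test statistics:
- any-visit error = 1 − P(all three Z < 1.645)
- all-visits power = P(all three Z < 0.825)
- any-visit power = 1 − P(all three Z < −0.825)

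| Correlation | Any visit: false non-inferiority | Any visit: power | All visits: power |
|---|---|---|---|
| 0 | 14.3% | 99.1% | 50.3% |
| 0.5 | 11.8% | 94.8% | 60.4% |
| 0.7 | 10.3% | 91.7% | 65.2% |
| 0.9 | 8.0% | 86.8% | 71.6% |

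The all-visits rule keeps error at or below 5%, because a false claim requires a false success at a visit where the true difference reaches the margin, and each visit is tested at 5%.

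**Step 4. Further loss after 12 months.** The article gives a single 10% allowance. Under Exclusion criteria, patients who move to risk level 3 at the 12- or 24-month assessment leave the study, at an unstated rate. As an illustration only, cumulative loss of 10%, 19% and 27.1% leaves 63, 56.7 and 51.0 per arm. Single-visit power is then 79.5%, 75.7% and 71.8%, and all-visits power is 43–66% over correlation 0 to 0.9.

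**Step 5. Size needed if all three visits must succeed.** For 80% overall power, 100, 92, 87 or 78 evaluable per arm are needed at correlation 0, 0.5, 0.7 or 0.9. With 10% dropout that is 223, 205, 194 or 174 in total.

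**The case against.** The best defence is that a lead visit can be inferred. The sample size is tied to 12 months in advance and the analysis section describes one interval, so the three-visit sentence could be read as a measurement schedule, with 24 and 36 months reported as follow-up. The study also calls itself proof-of-concept, and its sample size reproduces. This is a fair reading, and it is the one the fix adopts. But no sentence says it. Study data applies the words primary outcome to all three visits, and the Discussion states the hypothesis at all three.

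A second defence is that the way visits are combined, and their testing order, may sit in a statistical analysis plan that is not shown. That stands: the lack of a multiplicity procedure in the article is not a finding. Which visit is primary is a protocol matter, though, and the article's sections disagree on it.

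A reader might infer more than the document supports:
- **That neither the alpha nor the power can be achieved.** Each rule keeps one of the two, and a 12-month test keeps both.
- **That 140 is wrong.** It is about right for 12 months.
- **That the trial necessarily has three confirmatory tests, or that the visit will be chosen after the data are seen.** The article leaves the deciding visit open, but the sample-size section does point to 12 months.
- **That the computed percentages are properties of this trial.** They rest on an assumed correlation, and the error figures on a true difference at the margin at every visit.

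**Conclusion.** The point holds as an inconsistency in the text. Study data and the Discussion set the primary comparison at three visits, Population size calculation sizes the trial for one, and Statistical analysis does not name the deciding visit. Alpha 5% and power 80% hold together only for a single 12-month test (79.5% with 63 per arm).

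Under the three-visit definition, requiring all visits gives about 50–72% power with error at or below 5%. Accepting any visit gives 87–99% power with about 8–14% false non-inferiority. These ranges rest on equal correlation of 0 to 0.9 and 63 per arm at all visits; the error range also needs the true difference to equal the margin at every visit. Attrition after 12 months would lower the all-visits power further. The direction of the conclusion is the same across the whole range. It should be corrected because it determines what counts as success.

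**What to change.** 1. **Study data:** name HbA1c at 12 months as the single primary endpoint, as in the sample-size calculation, and list 24 and 36 months as secondary.
2. **Statistical analysis:** state that the 90% interval at 12 months decides non-inferiority.
3. **Discussion:** align the hypothesis to the same visit and the same quantity (mean or change).
4. **Later visits:** one option is a fixed sequence of 12, then 24, then 36 months, each at one-sided 5% and tested only if the previous visit succeeded. This costs no alpha at 12 months. The exact order may be placed in the statistical analysis plan.

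**Cost.** No more patients are needed and the text change is small. Recruitment had already begun in August 2015, so it should be made as a dated amendment before outcome data are compared by arm. The real price is that 36-month non-inferiority becomes secondary in a study meant to run for three years. Under the sequence it also depends on passing 12 and 24 months, and the chance of passing all three equals the all-visits power above, about 50–72% before further attrition. The sequence does not address the removal of patients who reach level 3, which affects who remains at the later visits.

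If the sponsor prefers all three visits as co-primary, that also resolves the contradiction, but the power must then be restated at about 50–72%, or the total raised to roughly 174–223.

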### Population size calculation

A power calculation was conducted according to criteria for non-inferiority trials [42, 43], and based on the primary outcome measure Hb_A1c_ at 12-month follow-up. The non-inferiority margin was set at 0.4 % (1 % is approximately 11 mmol/mol) based on both clinical judgement and a guideline from the European Medicines Agency identifying the non-inferiority margin for HbA_1c_ above 0.3 % (3 mmol/mol) [44]. The standard deviation of HbA_1c_ was set at 10 mmol/mol, based on a recent study on patients with risk stratification level 2 attending our outpatient clinic [31]. With a non-inferiority margin at HbA_1c_ 4.4 mmol/mol, an alpha of 0.05 and a power at 0.8, as well as an estimated dropout rate of 10 %, the sample size has been estimated to 140 participants.

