## Methods/Design

### Study design

The present trial is a proof-of-concept study. We aim to test the effect of a new model of organisation and management of diabetes care, and compare it with a standardised care management programme in a specialised outpatient clinic. The study is designed as a randomised controlled trial testing for non-inferiority between the two programmes. We hypothesise that patients with T2D followed in a shared care programme (intervention) will have a comparable primary outcome (HbA_1c_) compared to patients receiving standard care (control). The study flow is indicated in Fig. 1. The study follows the guidelines of Standard Protocol Items: Recommendations for Interventional Trials (SPIRIT) (Additional file 1).

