### Exclusion criteria

Patients are excluded if they have other types of diabetes than T2D, are at risk stratification level 1 or 3 (Table 1), are pregnant or breastfeeding, have severe co-morbidity with a life expectancy less than 5 years, or are under such conditions that they will not be able to attend or complete the appointments (e.g. due to dementia or psychiatric conditions). Furthermore, we will exclude patients who are either participating in other studies that potentially may affect the primary outcome of our study, or patients participating in studies which include blood sampling amounting to > 5 % of the blood volume in a 2 month period prior to the randomisation and/or the follow-up visits. The risk stratification level is assessed by the endocrinologist during the 12- and 24-months follow-up. If the patient has shifted from level 2 to level 3, the patient is excluded from the study. These patients will be offered long-term follow-up in the diabetes outpatient clinic. Patients changing from level 2 to level 1 will continue their participation in the study.

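### The 80% power behind 140 patients applies to 12 months only; 24 and 36 months have no stated power or visible allowance for level-3 removals, and the SD of 10 may be too low

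*Protocol article*

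**What the plan says.** The section Population size calculation bases the calculation on HbA1c at 12 months. It states "With a non-inferiority margin at HbA_1c_ 4.4 mmol/mol", then "an alpha of 0.05 and a power at 0.8, as well as an estimated dropout rate of 10" per cent, and concludes that "the sample size has been estimated to 140 participants". On variability it says "The standard deviation of HbA_1c_ was set at 10 mmol/mol", a value "based on a recent study on patients with risk stratification level 2 attending our outpatient clinic".

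Other sections bear on that figure:

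- Study data defines the primary outcome as the difference in mean HbA1c at 12, 24 and 36 months. All data are collected at the annual check-ups.
- Exclusion criteria has the endocrinologist reassess the risk level at the 12- and 24-month follow-up, and adds: "If the patient has shifted from level 2 to level 3, the patient is excluded from the study".
- Inclusion criteria (Table 1 and its notes) puts HbA1c above 75 mmol/mol in level 3. Level 2 requires at least one level-2 parameter and no level-3 parameter.
- Statistical analysis tests the primary outcome by "constructing a 90 % two-sided confidence interval for the difference of the means of HbA_1c" between the groups, with no mention of baseline HbA1c.

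**The concern.** The article gives one power figure, for the first of three primary time points. By 24 and 36 months the number of patients will have been reduced by ordinary dropout and also by a removal rule that the protocol itself imposes. Any one of the seven rows of Table 1 can trigger that rule. The sample-size text mentions only a dropout rate.

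The SD was estimated in patients selected to have no value above 75. Randomised patients meet that limit at baseline, but nothing holds their HbA1c below it afterwards. An SD from a sample cut off at the top tends to understate the spread of values free to pass the cut.

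In a non-inferiority trial, low power produces wide, inconclusive intervals. If readers take 80% to apply throughout, a failure to show non-inferiority at 24 or 36 months could be misread as evidence that shared care is inferior.

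**Working it through.** **Inputs from the protocol:** margin 4.4; SD 10; power 0.80; dropout 10%; 1:1 allocation. One-sided alpha is 0.05, because one bound of a 90% two-sided interval decides. **Assumed:** true difference 0, consistent with the hypothesis of a comparable outcome in Study design.

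**1. Reproducing 140**

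- n per arm = 2 × (1.645 + 0.842)² × 10² / 4.4² = 63.9, so 64 per arm and 128 in total.
- With 10% dropout: 128 / 0.9 = 142.2, so 143. Multiplying instead gives 128 × 1.1 = 140.8.
- In reverse: 140 × 0.9 = 126, or 63 per arm. Power = Φ(4.4 / (SD × √(2/n)) − 1.645) = Φ(4.4/1.782 − 1.645) = 79.5% (79.1% by noncentral t).

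So 140 agrees with the stated inputs to within three patients and about half a percentage point, for 12 months.

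**2. When removals take effect**

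The first reassessment of level takes place at the 12-month follow-up, where the 12-month HbA1c is also collected. No removal is scheduled before that measurement. If the value is kept, the rule costs no patients at 12 months. It reduces the numbers at 24 months, and again at 36.

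**3. Unadjusted power over assumed loss and SD (140 randomised)**

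| Total loss | per arm | SD 10 | SD 11 | SD 12 |
|---|---|---|---|---|
| 10% | 63 | 79.5% | 72.6% | 66.0% |
| 20% | 56 | 75.3% | 68.1% | 61.6% |
| 30% | 49 | 70.3% | 63.1% | 56.8% |

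As one example for 36 months, an assumed loss of 10% a year from all causes leaves 70 × 0.9³ = 51 per arm. Power is then Φ(4.4/1.980 − 1.645) = 71.8% with SD 10.

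**4. How far the cap at 75 could matter**

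Suppose HbA1c is normal but cut off at 75, with an observed SD of 10. Let s be the uncut SD and r the correlation between baseline and 12 months. The 12-month SD is then √(r² × 100 + s² × (1 − r²)). The observed means below and r = 0.5 are assumptions.

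| Observed mean | s | 12-month SD at r = 0.5 |
|---|---|---|
| 50 | 10.28 | 10.2 |
| 54 | 10.76 | 10.6 |
| 56 | 11.26 | 11.0 |
| 58 | 12.11 | 11.6 |
| 60 | 13.70 | 12.9 |

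The effect runs from negligible to large, depending on a mean that the article does not report.

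**5. Effect of adjusting for baseline HbA1c**

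ANCOVA replaces SD by SD × √(1 − r²). At an assumed r of 0.5 the factor is 0.866:

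- SD 10 (residual 8.66): 88.6% at 63 per arm, 82.1% at 51.
- SD 11 (residual 9.53): 82.8% at 63 per arm.
- SD 12 (residual 10.39): 76.8% at 63 per arm.

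At a weaker assumed r of 0.3 (factor 0.954) with SD 10, power is 82.7% at 63 per arm and 75.3% at 51.

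**The case against.** The strongest reply is that the calculation is sound for what it claims. It is expressly for 12 months, it reproduces, and no power is asserted for later visits, so nothing stated is contradicted. This stands. A reader might infer that 140 does not follow from the plan's inputs. It does; the gap between 140 and 143 is a matter of inflation and rounding.

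Second, a reader might add level-3 removals to the 10% dropout at 12 months. The timing does not support this, since it would require discarding an HbA1c taken at the same visit, and no section says that happens. Nor does the article say what the 10% covers. The supportable statement is that no allowance for removals is shown, not that they were certainly left out.

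Third, it is tempting to argue that 80% fails either way: remove level-3 patients and numbers fall, or keep them and the SD rises. The two effects partly offset each other. If patients above 75 are left out of the analysis, the analysed values carry the same cap as the SD source; if they are kept, no patients are lost. The offset is incomplete, because removal for blood pressure, cardiovascular, foot, eye or kidney criteria loses patients without capping HbA1c.

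Fourth, level 2 has no lower HbA1c limit, so the source mean may lie well below 75 and the cap may hardly bind. That is why the SD can only be said to be possibly too low.

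Finally, the clinic's case mix (54% at level 2, under 5% at level 1) leaves more than 41% at level 3. A reader might take this as a sign of frequent removal. It is cross-sectional prevalence in a hospital clinic, whereas the trial also recruits patients managed solely by their GP. It says nothing about the rate of moving from level 2 to level 3.

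**Conclusion.** The concern holds in a limited form. The sample size is right for 12 months, at 79–80% power, provided that the SD is 10 and that 12-month values are kept for patients then found at level 3. Beyond 12 months the article names two further primary time points and a rule that removes patients before them, with neither power nor a visible allowance. The SD comes from a sample cut off at 75 and may understate follow-up variability.

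The size of any shortfall rests on assumptions. Unadjusted power is about 72% at 51 per arm with SD 10, and 73% or 66% at 63 per arm with SD 11 or 12. The documents give neither the rate of moving to level 3 nor the follow-up SD, so no single corrected figure exists. The figures do not show that the trial is too small, since baseline adjustment could recover much or all of the loss.

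**What to change.** 1. In Population size calculation, claim about 79–80% power for 12 months only. State the two conditions (SD 10; 12-month HbA1c kept for patients found at level 3 at that visit) and what the 10% covers. Give power separately for 24 and 36 months over a stated range, for example 10–30% total loss and SD 10–12, with the expected rate of moving to level 3.
2. In Statistical analysis, base the 90% confidence interval on the difference in HbA1c adjusted for baseline HbA1c (ANCOVA) instead of the unadjusted difference of means. State the assumed correlation, since the gain depends on it.

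The cost is a rewritten paragraph with a less favourable headline figure and one changed sentence on the analysis. Baseline HbA1c is already collected, and no patients are added.
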